### Data monitoring and safety monitoring

The safety of participants will be reviewed; the CRFs and evidence documents will be compared for certification of completeness of data.

Monitoring will be scheduled for three timepoints: upon recruitment of study participants; in progress during the study period; and upon completion of the clinical trial. Monitoring sessions will be performed by the personnel responsible for monitoring at the supervising study site.

All AEs reported during the study period will be noted to calculate the incidence of AEs. The proportion of participants with AEs in each group will be calculated and compared using Chi-square test or Fisher’s exact test.

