### Objectives

This rigorous clinical trial was designed to the aim of determining the effectiveness, safety, and cost-effectiveness of Chuna manual therapy for chronic neck pain. First, the comparative effectiveness and safety of Chuna manual therapy will be evaluated through comparison of Chuna manual therapy and usual care as assessed using pain and functional indices as well as quality of life and adverse effect measures. In addition, analysis of long-term cost-effectiveness will examine the cost-effectiveness of Chuna manual therapy compared to usual care.

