### Sample size

Calculation of number of participants required for the clinical trial: for calculation of significant number of participants, the following is hypothesized based on the previous literature:Level of significance, α = 0.05;Type II error (β) is set at 0.2 with power of the test set at 80%;According to a previous clinical study using VAS as the main assessment tool for Chuna manual therapy in neck pain patients, the effect size of Chuna manual therapy in comparison to the control can be considered to be 1.03 [30], and 1.49 [31], respectively;Compliance rate will be set at 85% (the predicted rate of receiving ≥ 6 sessions of treatment during the five-week treatment period);For calculation of sample size, G*Power 3.1.7 was used. With evidence from item (3), application of mean ± SD resulted in conservatively hypothesizing the effect size of this clinical trial as 0.6 because of the high clinical heterogeneity of manual therapies such as Chuna. Application of items (1) and (2) and the effect size resulted in the calculation of a sample size of 90 participants (45 in each group).The mean comparison of pain requires a total of 90 participants (45 in each group), which is the minimum number of participants needed for testing the abovementioned hypothesis. Considering that 15% of participants received < 6 sessions of treatment within the five-week treatment period, a total of 108 participants, 54 in each group, will be extracted for the study.

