#### Subgroup analysis

Sociodemographic characteristics: body mass index, age (≥ 40 years; and < 40 years), sex, recommendations for surgery, driving, headache, depression, number of sick leave days from work;Physical examination: neurologic examination (sensory loss, muscle weakness), pain upon range of motion (ROM) (i.e. flexion, extension, lateral bending, rotation);Pain characteristics: area of neck pain (bilateral/unilateral, central/trapezius/back), existence of radiating pain (yes/no, unilateral/bilateral, pain under the elbow joint, pain in the back), pain characteristics (acute onset versus slow onset, persistent versus aggravating), conditions of pain aggravation (understress, fatigue), nocturnal pain;Treatment prior to study: experience of Chuna manual therapy, continuation of physical therapy or conventional medication;Expectancy and preference for treatment: credibility and expectancy, preference (Chuna manual therapy; usual care; or no preference);X-ray examination: head forward posture, lateral deviation of spine, cervical intervertebral disc space, degenerative change;Index severity evaluation: VAS ≥ 7 and < 7, NDI high/low.

All statistical analyses were performed with SAS version 9.4 statistical package (SAS Institute, Cary, NC, USA), with the level of significance set at *p* < 0.05.

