## Discussion

In previous studies of the effectiveness, safety, and cost-effectiveness of Chuna manual therapy for chronic neck pain, usual care was selected as the control group. While previous clinical studies only mention the term usual care for the treatment of neck pain [32, 33] or report diverse treatments such as physical therapy, analgesics or anti-inflammatory medication, NSAIDs, consultation with a general practitioner (GP), rest, exercise, education, manipulation, electrotherapy, and acupuncture treatment [34–39]. No specific direction for treatment is suggested and no unified guideline for diagnosis, management, or treatment is set. Therefore, rather than setting the control group at the evidence level of standard care, the researchers selected usual care consisting of treatment methods most frequently used in Korea as the control group. Korea employs a national healthcare social security system that is operated by the government; this is based on the national health insurance services that cover the entire South Korean population and its medical institutions. This system manages the approved medical fees with coverage of most medical conditions including neck pain; the HIRA database provides information on received treatments, medical services, and diagnosis [40]. The physicians administering usual care were provided with the most frequently prescribed types of treatment for neck pain from the 2014 HIRA-NPS data so as to place further external validity in selection of treatment approaches.

This RCT will investigate the comparative clinical effectiveness of Chuna manual therapy, a traditional Korean manual therapy, in comparison with the usual care widely used in Korea. However, by guaranteeing autonomy to the physicians as a pragmatic trial in selection of Chuna manual therapy techniques and usual care treatments, there are potential limitations in evaluating and interpreting the study results. This study will be the first well-designed, rigorous large-scale multicenter RCT, and will monitor safety with cost-effectiveness simultaneously. It is thereby expected to provide high-quality evidence of the safety and cost-effectiveness of Chuna manual therapy.

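### The only named between-arm method for adverse events is a chi-square or Fisher test in a trial sized on pain alone; a risk difference with a confidence interval would answer the safety objective better

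*Protocol article*

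**What the plan says.** Under Objectives, safety stands beside effectiveness: "the comparative effectiveness and safety of Chuna manual therapy will be evaluated through comparison of Chuna manual therapy and usual care". Under Data monitoring and safety monitoring, the comparison is specified as "The proportion of participants with AEs in each group will be calculated and compared using Chi-square test or Fisher’s exact test". The last sentence under Subgroup analysis covers all analyses, "with the level of significance set at" p < 0.05.

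The Sample size section concerns pain only. It gives "Level of significance, α = 0.05" and 80% power, and describes "conservatively hypothesizing the effect size of this clinical trial as 0.6", which leads to 45 per arm, later raised to 54.

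The Adverse events section adds that the frequencies of AEs, abnormal laboratory results and SAEs will be analysed, with severity and causality grading. It also says that occurrence will be analysed between groups, but names no method.

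On what the trial will deliver, the Discussion says: "It is thereby expected to provide high-quality evidence of the safety and cost-effectiveness of Chuna manual therapy".

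**The concern.** A chi-square or Fisher test asks whether the observed difference is larger than chance would explain. A safety objective asks something else: how much more harm could the new treatment cause, given these data? When the test is significant the two questions largely coincide. When it is not, the p-value leaves the second one unanswered, and in a trial sized on a continuous pain score that outcome can be likely even when the excess harm is real.

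The Discussion says that the results should inform practice guidelines and insurance coverage. If the safety comparison reaches those readers mainly as a non-significant test, they cannot see how large an excess the same data leave open. An interval would show it.

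**Working it through.** **1. The plan's own figure.** Inputs from Sample size: standardised effect 0.6, α = 0.05 (taken as two-sided), power 80%. For a two-sample t-test the required size is 44.6, so 45 per arm and 90 in total; power at 45 per arm is 0.804. This reproduces the plan's 90. Allowing for 15%: 45 / 0.85 = 52.9, so 53 per arm or 106 in total, close to the stated 108. No part of this calculation involves adverse events.

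**2. Chance of missing a doubled AE proportion.** Inputs: n = 54 per arm (the stated allocation), two-sided 0.05, and assumed AE rates, because the protocol gives none for either arm. With X ~ Bin(54, p₁) and Y ~ Bin(54, p₂), the miss rate is 1 − Σ P(X = x) P(Y = y) over all pairs (x, y) for which the test rejects. The lower figure uses chi-square, replaced by Fisher when an expected count is below 5. The upper figure uses Fisher throughout.

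| Usual care | Chuna | Missed |
|---|---|---|
| 5% | 10% | 89-93% |
| 10% | 20% | 70-79% |
| 15% | 30% | 53-63% |
| 20% | 40% | 37-45% |
| 25% | 50% | 22-28% |
| 30% | 60% | 12-16% |

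**3. The document's one background rate.** Background and rationale cites a study in which up to half of patients had adverse effects after manipulation. With Chuna set at that upper figure of 50%:

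| Usual care | Chuna | Excess | Missed |
|---|---|---|---|
| 25% | 50% | 25 points | 22-28% |
| 35% | 50% | 15 points | 66-72% |
| 40% | 50% | 10 points | 83-87% |

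**4. What an interval adds.** Suppose 11/54 against 5/54 (20.4% against 9.3%). Chi-square = (11 − 5)² × 108 / (16 × 92) = 2.64, p = 0.10; Fisher p = 0.17. Both are non-significant. The risk difference is 6/54 = 11.1 points, with a Newcombe 95% interval from −2.6 to +24.7 points. The same data thus leave open an excess of almost 25 points, which the p-value does not show.

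The approximate half-width is 1.96 × √[(p₁(1 − p₁) + p₂(1 − p₂)) / 54]. At 10% and 20% this is 1.96 × √(0.25 / 54) = 13.3 points. At 25% and 50% it is 1.96 × √(0.4375 / 54) = 17.6 points.

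**5. Serious events.** If no SAE occurs among 54 patients, the exact one-sided 95% upper bound is 1 − 0.05^(1/54) = 5.4%. The two-sided counterpart is 1 − 0.025^(1/54) = 6.6%.

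**The case against.** The case against is substantial. A chi-square or Fisher test on AE proportions is valid and common. Trials are routinely sized on the primary outcome, the Abstract lists adverse effects as secondary, and no AE power is claimed, so low power for AEs is not an error in itself. Only a journal article is at hand; an interval may be specified in the full protocol or analysis plan, so its absence here is weak ground on its own. All of this stands, and it keeps the point minor.

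Three stronger readings are tempting, and the document does not support them.

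- A reader might infer that p > 0.05 will be taken as proof of safety. The protocol says this nowhere. The nearest it comes is the expectation in the Discussion.
- A reader might infer that a p-value is all that will be reported. In fact the proportion in each arm is to be calculated, and AE, laboratory and SAE frequencies are to be analysed with severity and causality. A reader could compute an interval from the proportions.
- A reader might take a miss rate of 70-79% as a property of 54 per arm. It belongs to a control rate near 10%. From about 20% upward, a doubling is detected more often than missed.

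The objection does not remove the mismatch between the method named and the objective set. The article itself states both the test and the safety claim. The high background rate does not rescue the test either: at 50% in the Chuna arm, excesses of 10 to 15 points are still usually missed.

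**Conclusion.** The point holds as a minor, cheap improvement. The named safety comparison is a difference test in a trial sized on pain, and a non-significant result from it would not show how much excess harm is still compatible with the data.

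The size depends on the unknown AE rate. The miss rate for a doubling falls from 89-93% at a 5% control rate to 22-28% at 25% and 12-16% at 30%. For a 50% Chuna rate and an excess of 10 to 15 points it is 66-87%. These figures assume all 54 patients per arm are analysed, a two-sided 0.05 level, and the AE rates shown, none of which the protocol gives as an expected rate for a trial arm.

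**What to change.** In Data monitoring and safety monitoring:

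- Make the safety comparison the between-arm risk difference in participants with AEs, with a two-sided 95% confidence interval (for example Newcombe).
- Give an exact upper confidence bound for the SAE proportion in each arm.
- Keep the chi-square or Fisher p-value as descriptive.
- State that the safety conclusion will rest on the interval and that a non-significant test will not be read as evidence of equal safety.

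In the Discussion, moderate the safety sentence to match: the trial can estimate common AEs with limited precision, and even with no SAE in an arm of 54 it could not exclude an SAE rate below about 5%.

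The cost is a few sentences, with no new data and no more patients. The downside is a visibly wide interval and a more modest safety claim.

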### Stopping rules

It will be noted whether study participants completed the study; when treatment or observation is suspended, the reason will also be recorded. For participants who have been suspended from study, follow-up observations may be continued with the participant’s consent. Circumstances that disable further continuation of study participation include SAEs, detection of disease(s) that may potentially affect the study results, and withdrawal of participant consent for study participation.

## Discussion

In previous studies of the effectiveness, safety, and cost-effectiveness of Chuna manual therapy for chronic neck pain, usual care was selected as the control group. While previous clinical studies only mention the term usual care for the treatment of neck pain [32, 33] or report diverse treatments such as physical therapy, analgesics or anti-inflammatory medication, NSAIDs, consultation with a general practitioner (GP), rest, exercise, education, manipulation, electrotherapy, and acupuncture treatment [34–39]. No specific direction for treatment is suggested and no unified guideline for diagnosis, management, or treatment is set. Therefore, rather than setting the control group at the evidence level of standard care, the researchers selected usual care consisting of treatment methods most frequently used in Korea as the control group. Korea employs a national healthcare social security system that is operated by the government; this is based on the national health insurance services that cover the entire South Korean population and its medical institutions. This system manages the approved medical fees with coverage of most medical conditions including neck pain; the HIRA database provides information on received treatments, medical services, and diagnosis [40]. The physicians administering usual care were provided with the most frequently prescribed types of treatment for neck pain from the 2014 HIRA-NPS data so as to place further external validity in selection of treatment approaches.

This RCT will investigate the comparative clinical effectiveness of Chuna manual therapy, a traditional Korean manual therapy, in comparison with the usual care widely used in Korea. However, by guaranteeing autonomy to the physicians as a pragmatic trial in selection of Chuna manual therapy techniques and usual care treatments, there are potential limitations in evaluating and interpreting the study results. This study will be the first well-designed, rigorous large-scale multicenter RCT, and will monitor safety with cost-effectiveness simultaneously. It is thereby expected to provide high-quality evidence of the safety and cost-effectiveness of Chuna manual therapy.

This study will examine the effectiveness, safety, and cost-effectiveness of Chuna manual therapy which will provide an evidence base for clinical practice guidelines of Korean medicine and data towards strengthening coverage of healthcare services within the national health insurance system. It is also hoped to serve as reference for clinical trials in the study of acute or sub-acute neck diseases indicative of Chuna manual therapy.

### Trial status

The study will be initiated in October 2017 and participant recruitment is expected to be completed by June 2018. The study is expected to be completed by August 2019.

## Abbreviations

ANCOVA: Analysis of covariance
AUC: Area under the curve
EQ-5D-5 L: 5-level version of EuroQol-5 Dimension
EQ-VAS: EuroQol Visual Analogue Scale
HIRA-NPS: National Patient Sample of the Korean Health Insurance Review & Assessment Service
iCReaT: Internet-based Clinical Research and Trial management system
IRB: Institutional Review Board
ITT: Intention-to-treat
LOCF: Last observation carried forward
NDI: Vernon–Mior Neck Disability Index
NPQ: Northwick Park Neck Pain Questionnaire
NRS: Numeric Rating Scale
NSAID: Non-steroidal anti-inflammatory drug
PGIC: Patient global impression of change
PP: Per-protocol
RCT: Randomized controlled trial
RM ANCOVA: Repeated measure analysis of covariance
ROM: Range of motion
SF-12: 12-Item Short-Form Health Survey
SF-36: Short Form-36 Health Survey
SOP: Standard operating procedure
SPIRIT: Standard Protocol Items: Recommendations for Interventional Trials
VAS: Visual analogue scale
WPAI: Work Productivity and Activity Impairment questionnaire
